## 1. Abstract

The majority of acute, short-term opioid tablets prescribed following surgery go unused. In a recent analysis of post-operative orthopedic and urologic surgery data at 7 days >60% of tablets were left unused, and patients reported no intention of using them, by post-operative day 7. Disposal of unused opioid medications is important to limit diversion, misuse, and conversion to new persistent use. These are salient to the patient and others around them including children, family and friends. Though patients can flush their unused opioids, early research has shown that providing patients with disposal techniques can improve proper disposal rates. In this proposal we seek to test, through a randomized clinical trial, if providing patients with an opioid disposal kit at key post-operative times can improve the rate of self-reported disposal as compared with usual care. Using an established, automated system our primary outcome will be self-reported opioid disposal rates. We will conduct a prospective RCT amongst patients undergoing urologic surgeries, neurosurgeries, and orthopedic surgeries.

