## **5. Study design**

### *5.1 Design*

This is a two-arm, randomized, controlled trial. The study will be conducted using an automated, remote text messaging platform (Way to Health) which delivers text messaging following orthopedic, neurosurgical, and urology procedures at the University of Pennsylvania.

The study team will identify potential participants from the electronic health record at the University of Pennsylvania Health System using Penn Data Store and Clarity, an EPIC reporting database. Patients undergoing a procedure in neurosurgery, orthopedics, or urology and who are prescribed an acute opioid will receive a text message four days following their discharge. This established system obtains remote, text-messaged based consent on post-operative day four. For those consenting, patients are queried on self-reported pain intensity, ability to manage pain, use of non-opioid analgesics, use of opioid analgesics, and opioid disposal. Once a participant responds and consents on day four, the participant will be mailed an opioid disposal kit which includes an informational sheet and the chemical packet (DispoRx).

Participants will be randomly assigned to intervention or control according to calendar week of surgery in alternating weeks over a 6-week period. Participants randomized to the control arm will receive no other interventions.

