### *5.2 Study duration*

This is 6-week study.

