### *5.4 Accrual*

We estimate that a sample size of 250 participants (125 per arm) will provide at least 80% power using a conservative Bonferroni adjustment of the Type I error rate with a 2-sided  $\alpha$  of 0.025 to detect a 20% change in disposal rates. Preliminary data suggest a baseline rate of 25%.

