### *8.2 Procedures*

After providing informed consent, participants will be sent messaging on post-operative days 4, 7, 14, 21, and 28. At each time point, patients are asked to self-report pain intensity (scale 0-10, 10 being severe), ability to manage pain (scale 0-10, 10 being very able to manage), and use of non-opioid and opioid analgesics. Patients who are using opioid analgesics are asked to report quantity used, projection of future use for acute pain. Patients reporting no further use are asked about disposal (Yes or No).

Patients will be mailed opioid disposal packets, DispoRx, which are small chemical polymers which individuals can pour directly into a pill bottle. The individual shakes the bottle and the medication is deactivated, rendered unusable and can be placed safely in the trash. We will mail these packets to individuals within the first 7 days for Orthopedic and Urology and timed for 21 days for Neurosurgery.

145 Participants will be randomly assigned at the individual level to receive a disposal packet. Participants  
146 randomized to the control arm will receive no other interventions.

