## 147 **9. Analysis plan**

148 To compare sample characteristics between arms we will use t-tests or Wilcoxon rank-sum tests (F-tests or  
149 Kruskal-Wallis test) for continuous variables and Pearson chi square tests or Fisher's exact tests for categorical  
150 variables. In our primary analyses, we will compare rates of opioid disposal (baseline vs. 6-week study period).  
151 In the secondary analysis we will compare self-reported pain intensity, ability to manage pain, and opioid use.  
152 All hypothesis tests will be two-sided using a two-sided alpha of 0.025 as our threshold for statistical  
153 significance. We will use Stata and/or SAS to analyze the data.

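### Section 9 states the primary analysis as baseline versus a 6-week period, not intervention versus control, and names no post-operative assessment day

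*Supplement*

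**What the plan says.** Section 9 defines the primary analysis in one sentence: "In our primary analyses, we will compare rates of opioid disposal (baseline vs. 6-week study period". The sentence names no arm, test, effect measure or post-operative day. The phrase about arms in that section belongs to a different task: "To compare sample characteristics between arms we will use t-tests or Wilcoxon rank-sum tests".

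Other sections describe a comparison of two arms:
- The abstract asks whether the kit "can improve the rate of self-reported disposal as compared with usual care", and the background repeats the question.
- Section 5.1 describes a two-arm randomised controlled trial.
- Section 5.4 says "a sample size of 250 participants (125 per arm) will provide at least 80% power" and gives the protocol's only baseline figure: "Preliminary data suggest a baseline rate of 25" per cent.

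On time, section 5.2 says "This is 6-week study". Section 5.1 says "Participants will be randomly assigned to intervention or control according to calendar week of surgery in alternating weeks over a 6-week period". Section 8.2 says "participants will be sent messaging on post-operative days 4, 7, 14, 21, and 28". Section 3.1 names the outcome as the self-reported disposal rate, without a day.

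**The concern.** The analysis section is where the primary contrast is fixed, and here it fixes one that the trial was not designed to make. Comparing the study period with an earlier rate makes no use of random assignment. Any change in disposal since the preliminary data, whatever its cause, would be credited to the kit. If both arms are pooled in the study period, a real kit effect is also diluted by the controls.

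The missing assessment day adds a second freedom. Disposal can be reported at any of five messages, and only by those who reach the question. Two analysts could therefore count different reports, over different denominators, and obtain different rates from the same data.

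**Working it through.** **1. What baseline can mean.** Section 8.2 puts the disposal question only to patients who say they no longer use the opioid. In the message script, the question (Q9) is reached only after the patient has taken the drug (Q5), has pills left (Q7) and does not plan to continue (Q8). There is no disposal value for each participant before the intervention. The only figure in the protocol that fits the word is the 25% in section 5.4, so read literally the sentence is a comparison with an earlier rate.

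**2. What 6 weeks can mean.** Section 5.1 attaches 6 weeks to assignment by week of surgery. If the 6 weeks also had to contain 28 days of follow-up, only 42 − 28 = 14 days would remain for surgeries, against the six weeks in section 5.1. So 6 weeks most naturally means enrolment. The last day-28 message then falls on day 42 + 28 = 70, or calendar week 10. For any one participant, day 28 is the end of week 4. On this reading the durations do not conflict, but no outcome day has been stated.

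**3. The plan's own power figure.** Inputs from sections 5.4 and 9: 125 per arm, 25% baseline, a 20% change and two-sided alpha 0.025 (z = 2.241). The change is read as absolute, 25% to 45%; read as relative (25% to 30%), power would be only 8.7%. For a between-arm z test with pooled variance under the null:
- SE0 = √(0.35 × 0.65 × 2/125) = 0.0603
- SE1 = √((0.25 × 0.75 + 0.45 × 0.55)/125) = 0.0590
- Power = Φ((0.20 − 2.241 × 0.0603)/0.0590) = Φ(1.098) = 86.4%

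This reproduces the stated 80% or more. It is a between-arm calculation, which is further evidence of the intended contrast. It assumes independent participants, all evaluable.

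**4. Dilution under the literal reading.** Assume pooled equal arms compared with 25%, and a kit that works as planned. The pooled rate is (25% + 45%)/2 = 35%, so the contrast shown is 35 − 25 = 10 points instead of 20.

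**5. False attribution under the literal reading (illustrative only).** Assume the kit does nothing, both arms sit at 30% or 35% for other reasons, and all 250 participants are pooled. The probability of significance at 0.025 in favour of the study period is:

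| Comparator (assumed) | Both arms 30% | Both arms 35% |
|---|---|---|
| 25% taken as fixed | 35% | 90% |
| Baseline sample of 250 | 16% | 58% |
| Baseline sample of 100 | 9% | 33% |
| Baseline sample of 50 | 6% | 18% |

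For the first row, SE0 = √(0.25 × 0.75/250) = 0.0274, so the cut-off is 0.25 + 2.241 × 0.0274 = 31.1%. The other rows use the two-sample test from step 3. With equal arms and independent participants, the between-arm test rejects 2.5% of the time, counting both directions.

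**The case against.** The strongest reply is that the intent is plain. The design is a two-arm randomised trial, the question is kit against usual care, and the sample is sized per arm. No section says that the arms will be pooled or that a historical group is the comparator. On this view the parenthesis in section 9 is a slip. That stands as to intent. A reader might infer that the arms would never be compared, and the documents do not support that. It does not repair section 9, which states a different contrast and is corrected nowhere else.

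A reader might also infer that a 6-week study contradicts follow-up running to week 10. Step 2 shows that it need not: section 5.1 ties the 6 weeks to surgeries, and week 10 is calendar time for the last entrants only. What stands is the missing assessment day.

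The percentages in step 5 are open to the objection that they rest on pooling, drift and a baseline size that the documents do not give. This is right. The range from 6% to 90% comes from those assumptions, so the table shows the direction of the risk, not its size.

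Finally, 86% power and 2.5% error are not guaranteed for the between-arm test:
- Section 5.1 assigns by alternating week, while section 8.2 assigns individuals. If weeks are the unit (about 250/6 ≈ 42 participants each), an assumed intraclass correlation of 0.01 to 0.02 gives a design effect of 1.41 to 1.81. An unadjusted test then has a type I error of about 6% to 10%. Dividing the sample by the design effect puts power at about 71% to 59%.
- If only 75 per arm were evaluable (assumed), power would be about 63%.

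**Conclusion.** The point holds in this form: the primary comparison is wrong as written and has no assessment day, although the intended comparison is probably between arms. It should be corrected before analysis.

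The mismatch itself rests on the text alone and needs no assumption. The halving from 20 to 10 points assumes pooled equal arms, the 25% as comparator and an absolute 20-point effect. The figure of 86% shows that the planned sample was computed for the between-arm test; it does not show that the power will be achieved. The documents do not support a claim that the trial would ignore its control arm, that its durations are incompatible, or that any particular false-positive rate applies.

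**What to change.** In section 9, replace the parenthesis with: *the proportion reporting disposal at or before each participant's own post-operative day-28 message, compared between the randomised intervention and control arms*.

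State one denominator rule for both arms. One option is all randomised participants, with those not asked or not responding counted as not disposed, and a sensitivity analysis among those asked the disposal question. State also whether the 25% in section 5.4 uses the same denominator, since the power figure depends on it. Name the test and the effect measure.

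Keep any comparison with the 25% preliminary rate as descriptive. In section 5.2, say that 6 weeks is enrolment and that each participant is followed to day 28, about 10 calendar weeks in all.

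The cost is a change to the stated primary comparison. It needs no more participants, since section 5.4 already sizes per arm. It needs no more messages if the section 8.2 schedule applies to everyone. The script promises another text in a week only to patients who plan to continue the opioid, so confirm that patients who have stopped but not yet disposed are asked again.

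### Surgical service is left out of both the assignment and the primary comparison; if service predicts disposal, this gives up some precision

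*Supplement*

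**What the plan says.** Section 5.1 defines the population by three services: "Patients undergoing a procedure in neurosurgery, orthopedics, or urology" who are prescribed an acute opioid. Section 8.2 treats the services differently: "We will mail these packets to individuals within the first 7 days for Orthopedic and Urology and timed for 21 days for Neurosurgery". The same section sets the follow-up: "participants will be sent messaging on post-operative days 4, 7, 14, 21, and 28".

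Assignment is described twice. Section 5.1 allocates by calendar week of surgery, alternating over six weeks. Section 8.2 allocates by individual. Neither mentions strata.

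Section 9 gives the primary analysis in one sentence, "we will compare rates of opioid disposal (baseline vs. 6-week study period", and names no test, model, stratum or covariate. It plans tests of sample characteristics between arms but does not say how the results would be used. The threshold is "two-sided using a two-sided alpha of 0.025".

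Section 5.4 says that "a sample size of 250 participants (125 per arm) will provide at least 80% power" "to detect a 20% change in disposal rates", from a single overall baseline rate of 25%. No control disposal rates on a common basis are given by service, and no service shares.

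**The concern.** Service follows from the procedure found in the health record, so it should be known for everyone before assignment. Leftover tablets and willingness to discard them plausibly differ between services. If they do, a pooled comparison carries between-service variation that a stratified one removes, and a chance excess of one service in one arm moves the estimate with nothing to correct it. Because no adjustment is prespecified, any adjustment for service would be chosen after the data are seen.

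Kit timing is a related but separate matter. A neurosurgery kit timed for day 21 leaves 28 − 21 = 7 days before the last message, while a kit mailed by day 7 leaves at least 28 − 7 = 21. The effect may therefore differ by service, and a single pooled difference would depend on the service mix without showing it.

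**Working it through.** **Inputs from the protocol.** 125 per arm and a 25% baseline (5.4); two-sided alpha 0.025 (5.4 and 9), so z = 2.2414. The 20% change is read as 20 percentage points, 25% to 45%. Read as a relative change (25% to 30%), power at 125 per arm would be 8.7% and 1,515 per arm would be needed, which does not fit 250.

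**Assumed, not in the documents.** Equal thirds by service, control rates averaging 25%, the same 20-point effect in each service, individual 1:1 assignment, and a disposal answer from everyone.

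**Step 1: the plan's own figure.**
- Null SE = √(2 × 0.35 × 0.65 / 125) = 0.0603.
- Alternative SE = √((0.25 × 0.75 + 0.45 × 0.55) / 125) = √(0.435 / 125) = 0.0590.
- Power = Φ((0.20 − 2.2414 × 0.0603) / 0.0590) = Φ(1.098) = 86.4%.

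The claim of at least 80% holds.

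**Step 2: stratify by service.** Replace each variance by the average within-service variance. For control rates of 10/25/40% (intervention 30/45/60%):
- Control: (0.09 + 0.1875 + 0.24) / 3 = 0.1725.
- Intervention: (0.21 + 0.2475 + 0.24) / 3 = 0.2325.
- SE = √(0.405 / 125) = 0.0569; variance reduction = 1 − 0.405 / 0.435 = 6.9%.
- Null SE, at service averages 20/35/50%: √(2 × 0.2125 / 125) = 0.0583.
- Power = Φ((0.20 − 2.2414 × 0.0583) / 0.0569) = Φ(1.218) = 88.8%.

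The same formulas over a range, with simulated power (20,000 runs each, unstratified assignment, pooled z-test against Mantel-Haenszel test):

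| Control rates by service | Variance reduction | Stratified power, formula | Simulated power, crude → stratified |
|---|---|---|---|
| 25/25/25% | 0% | 86.4% | 86.5% → 86.0% |
| 15/25/35% | 3.1% | 87.5% | 86.8% → 87.5% |
| 10/25/40% | 6.9% | 88.8% | 86.4% → 88.5% |
| 5/25/45% | 12.3% | 90.7% | 86.9% → 90.7% |

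With unequal shares of 60/25/15% and control rates of 30/22/10% (also assumed), the reduction is 2.3% and power 87.2%.

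**Step 3: validity of the unadjusted test.** With no effect, its simulated type I error was 0.022 to 0.027 against the nominal 0.025. Both estimators averaged within 0.1 point of the true difference.

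**Step 4: chance imbalance.** For a service holding one third of patients, the between-arm difference in share has SD √(2 × (1/3) × (2/3) / 125) = 0.0596. The chance of a gap of 10 points or more is 2 × (1 − Φ(0.10 / 0.0596)) ≈ 9%. The shift in the crude difference is the sum over services of (difference in share × control rate). At 10/25/40%, with a 10-point excess in the 40% service:
- offset evenly by the other two: 0.10 × 40 − 0.05 × 25 − 0.05 × 10 = 2.25 points;
- offset wholly by the 10% service: 0.10 × (40 − 10) = 3 points;
- offset wholly by the 25% service: 0.10 × (40 − 25) = 1.5 points.

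A 10-point excess in the 25% service, offset evenly, gives 0.10 × 25 − 0.05 × 40 − 0.05 × 10 = 0.

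**The case against.** The strongest reply is that no stated property of the design fails. Crude power is about 86% in every scenario, the test keeps its size, and chance shifts in service mix are already covered by the unadjusted standard error. The gain rests on invented service rates and vanishes if service is not prognostic. All of that stands, and it makes this a modest point. Two things limit it. The change costs almost nothing. And the 86% presumes 250 disposal answers, whereas the text-message script puts the disposal question (Q9) only to patients who took the opioid, have pills left and plan no further use. If, say, 94 per arm answered (an assumption), the same formulas give 74% crude and 77% stratified at 10/25/40%.

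A second reply is that section 9 never states a crude comparison of arms. This is right. Its wording sets baseline against the study period and names no test, so the undefined contrast is the larger fault and has to be settled first. Service is absent whichever contrast is meant.

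A third is that the imbalance figures and permuted blocks presuppose individual assignment. This also stands. Under alternating weeks, with about three weeks per arm, service mix could be more uneven than Step 4 suggests, and adjusting for service would not deal with week effects.

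A reader might infer from the kit timing that pooling is shown to lose precision. It is not. Timing bears on whether the effect differs by service, and the calculations above hold the effect constant.

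**Conclusion.** The omission is real: three services with different kit timing are pooled, and service appears in neither assignment description nor in the primary analysis. The consequence is conditional. If service predicts disposal, adjustment would cut the variance by up to about 12% and add up to about 4 points of power over the assumed range; if not, it changes essentially nothing. A 10-point imbalance in the highest-rate service would move the crude difference by about 2 to 3 of the 20 points sought at 10/25/40%, and less under milder patterns.

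Stronger readings are tempting: that the unadjusted result would be biased, that the trial is underpowered for this reason, or that the services are known to differ. The documents support none of them. Under individual assignment the crude test is valid and, with complete answers, above its 80% target. The Background's one neurosurgery figure (64% with excess tablets not disposed of) has no counterpart on the same basis for the other two services.

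**What to change.** - **Section 9.** State the primary contrast as intervention versus control. Test it with a Mantel-Haenszel comparison stratified by service, or logistic regression with arm and service. Report the service-standardised risk difference with its confidence interval.
- **Section 9, alongside.** Report the three service-specific differences with intervals. A common-effect estimate cannot show whether the short time between a day-21 kit and the day-28 message matters in neurosurgery.
- **Sections 5.1 and 8.2.** Reconcile alternating weeks with individual assignment. If assignment is individual, stratify it by service with permuted blocks. If it is by week, adjusting for service does not cure the week-level allocation, which needs its own treatment.

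The cost is a few lines of text, with no new data and no change in sample size. The protocol does not say where the assignment is generated, so the effort of stratifying it cannot be judged from the documents. If service turns out not to be prognostic, the loss is negligible (simulated power 86.0% against 86.5%).

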### *3.2 Secondary outcome*

The secondary outcome is self-reported number of opioid tablets used following surgery.

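### The Bonferroni level of 0.025 names no family of tests: it costs the single primary outcome about 5 points of power, yet does not hold 5% over the four outcomes in section 9

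*Supplement*

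**What the plan says.** Section 3.1 names one primary outcome, the rate of self-reported opioid disposal. Section 3.2 names one secondary outcome: "The secondary outcome is self-reported number of opioid tablets used following surgery".

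Section 5.4 plans 250 participants, 125 in each of two arms, for at least 80% power against a 20% change from a baseline disposal rate of 25%. It sets the level at two-sided 0.025, "using a conservative Bonferroni adjustment of the Type I error rate". It does not say which tests the adjustment covers.

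Section 9 carries the level to everything: "All hypothesis tests will be two-sided using a two-sided alpha of 0.025". After the disposal comparison it adds: "In the secondary analysis we will compare self-reported pain intensity, ability to manage pain, and opioid use". It gives no testing order, does not call the secondary tests exploratory, and names no time point, model or covariate for them.

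On data collection, section 8.2 has pain intensity, ability to manage pain and analgesic use asked on days 4, 7, 14, 21 and 28. Section 5.1 has the kit mailed only after the day-4 response and consent.

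**The concern.** A Bonferroni correction is defined by the set of tests that it covers. With two arms and one primary outcome, the primary test needs no division. A divisor of 2 makes sense if the family is the primary plus the single secondary of section 3.2, but section 9 lists four outcomes at the same level. The plan thus pays for a correction on its main question and does not get 5% control over the tests to which it applies it.

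The two lists of secondary outcomes also disagree. Pain intensity and ability to manage pain appear only in section 9, and the opioid use named there is not tied to the tablet count of section 3.2. That leaves room to choose, after the data are seen, which result is reported as the secondary finding.

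A smaller matter is precision. Day-4 pain scores are collected before any kit is mailed, and the plan is silent on using them.

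**Working it through.** **Inputs.** Control rate 0.25, 125 per arm, two-sided 0.025 and the 80% power target come from section 5.4. The 20% change is read as 20 percentage points (25% versus 45%). The relative reading, 25% versus 30%, would give only 8.7% power, so it cannot be what was meant. Outcomes are counted from sections 3.1, 3.2 and 9.

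**1. The plan's own figure.** Power = Φ[(d − z·SE0)/SE1], with d = 0.20 and mean rate 0.35.
- SE0 = √(2 × 0.35 × 0.65/125) = 0.0603
- SE1 = √((0.25 × 0.75 + 0.45 × 0.55)/125) = 0.0590
- At 0.025, z = 2.241: (0.20 − 0.1352)/0.0590 = 1.10, power **86.4%** (83.2% with continuity correction).

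The stated minimum of 80% is reproduced. The number needed for 80% is 107 per arm (214), or 117 per arm (234) with continuity correction, so 250 is above the requirement.

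**2. Cost of the adjustment to the primary test.**
- At 0.05, z = 1.960: (0.20 − 0.1182)/0.0590 = 1.39, power **91.7%**.
- Loss: 91.7 − 86.4 = **5.3 points**.
- Number needed for 80% power at 0.05: 89 per arm (178), against 214 in total at 0.025.
- Detectable difference at 80% power with 125 per arm: about 16.7 points at 0.05, about 18.5 at 0.025.

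**3. What the adjustment covers.** For m tests at 0.025 the family error is at most 0.025m under any dependence, and 1 − 0.975^m if the tests are independent.

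| Family | m | Bound | If independent |
|---|---|---|---|
| Outcomes of section 3 | 2 | 5.0% | 4.9% |
| Outcomes of section 9 | 4 | 10.0% | 9.6% |

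A Bonferroni correction over four tests would use 0.0125 each. Primary power would then be 79.8%, so enlarging the divisor does not help the primary test.

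**4. Day-4 score as a covariate.** Adjusting for a pre-kit value correlated r with the later one cuts residual variance by r². No correlation is given in the documents. For assumed r of 0.3, 0.5 and 0.7 the cut is 9%, 25% and 49%.

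**5. Can tablets used be adjusted in the same way?** In the text-message script at the end of the document, Q6 asks for pills taken since the procedure, which is a cumulative count. Under Q8, a further text in one week is scheduled only for patients who plan to keep taking the opioid. Section 8.2 implies messages to everyone at every time point. If the script governs, a patient who reports no further use on day 4 has no later count, so the day-4 count is that patient's outcome. Using it as a covariate would then put the outcome on both sides of the model.

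**The case against.** The strongest defence is that nothing here endangers the primary conclusion. The level of 0.025 is stricter than 0.05, the trial was sized for it, and power exceeds the stated target. All of that stands.

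Nor do the documents promise 5% across all secondary outcomes, and many trials do not seek it. That is fair as far as it goes. But the plan itself invokes Bonferroni and applies the level to all tests, so it is reasonable to ask what the correction achieves. The 9.6% figure does assume independence, which is unlikely for pain, pain management and opioid use. With positive correlation the true error would be lower. The claim is only that 5% is not guaranteed and that 10% is the bound.

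Opioid use in section 9 may well mean the tablet count of section 3.2. The mismatch is then two additional outcomes, not three.

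The silence on day-4 values is an omission and not a decision to ignore them. No separate SAP is shown, and covariates are often left to one. An unadjusted comparison of properly randomised arms remains valid, so only precision is at stake.

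A reader might infer that the trial is underpowered. The documents do not support that. The 50–60% response rate in section 8.1 belongs to the existing messaging programme and is not a loss among consenting participants. The script does put the disposal question only to patients who took the opioid, have pills left and plan no further use, so fewer than 125 per arm may be evaluable, but no number is given. Purely as assumptions, 100 evaluable per arm would give 77.0% power at 0.025 and 84.8% at 0.05; 75 per arm would give 63.1% and 73.3%.

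**Conclusion.** The point holds as inefficiency together with a correction that does not cover the tests listed. The primary outcome loses 5.3 points of power (86.4% against 91.7%), while the error over the four section 9 outcomes is bounded by 10% instead of 5%. Two of those outcomes are missing from section 3.2.

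A reader might go further and conclude that the primary result is exposed to inflated error. It is not: that test is held at 0.025, and the 10% refers to the whole set of four.

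The power figures assume a 20-point difference, all 125 per arm evaluable, independent participants and a between-arm comparison. Each outcome is counted once. Section 9 fixes no time point, so the number of tests could be larger, but the conclusion does not depend on that. The day-4 adjustment is a modest gain of unknown size, and it is safe for pain scores but not necessarily for tablet counts.

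**What to change.** 1. Test disposal at two-sided 0.05. Only if it is significant, test tablets used at two-sided 0.05. This fixed sequence holds 5% over both: if the primary null is true, any error requires rejecting it first; if it is false, only the secondary test can err. Amend sections 5.4 and 9 to match and remove the Bonferroni statement.
2. Report pain intensity and ability to manage pain as estimates with confidence intervals and no confirmatory claim.
3. List the same secondary outcomes in sections 3.2 and 9, and define opioid use as the tablet count if that is meant.
4. Adjust post-kit pain scores for the day-4 score and for specialty. State which time points count as post-kit, because section 8.2 gives a later mailing time for neurosurgery than for the other two specialties.
5. Do not adjust tablets used for the day-4 count unless later counts are collected for all participants. Reconcile section 8.2 with the script on this.

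If the sponsor prefers to keep 0.025, naming disposal and tablets used as the whole family would also be valid, but it keeps the 5.3-point loss.

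The cost of items 1 to 4 is wording, with no added patients or questions. The downside is that tablets used can support a confirmatory claim only if disposal succeeds. If the script does stop texting some participants early, obtaining later tablet counts from everyone would be an operational change as well.
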